**Figure 2 figure2:**
[figure not shown]
Bizi Orain exercise program. M1: Low-to-moderate intensity; M2: moderate intensity; M3: intensive moderate intensity; WUp: warm up.

**Table 1 table1:** Definitions of exercise intensity categories.

Zone^a^	%HRR^b^	RPE^c^	Training type
High-intensity training	>85	>5.5	High-intensity training. The patient nears exhaustion and is no longer in a steady state.
M3	60-84	4.5-5.5	Intensive moderate intensity. The patient has difficulties in talking and sweating increases.
M2	40-59	3-4	Moderate intensity. The patient notices an increased respiratory rate.
M1	20-39	1-2.5	Low-to-moderate intensity. The patient does not notice any increase in the respiratory rate.
Low-intensity training	<20	<1	Low intensity. This involves daily activities requiring low levels of effort.

^a^The intensity zones are based on the estimated maximum heart rate and applying specific intensity boundaries based on HRR [27]. RPE (determined using the Borg scale from 0 to 10) [28].

^b^HRR: heart rate reserve.

^c^RPE: rating of perceived effort.

The resistance component involves exercises that target six of the major upper and lower body muscle groups, as well as core exercises using exercise machines, bars, free weights, dumbbells, ankle weights, elastic bands, material for suspension training, and fitness balls. A progression from static exercises toward more dynamic exercises is encouraged, aiming to activate more muscle mass and thereby increase the cardiovascular demand. Among the main resistance exercise parameters that can be modified, the actual number of repetitions performed in a set, in relation to the maximum number that can be completed (ie, proximity to muscle failure), recently called “level of effort,” will be used to individualize the resistance exercise intensity, maximize the suitability of the exercise for each patient, and optimize the induced neuromuscular fatigue [46,47]. The target intensity is adjusted from 9 to 12 repetitions out of the 18 repetitions that could be completed (written as 9-12 (18)), which is equivalent to ~60% of 1 repetition maximum (1RM) using 2-3 sets during the first 4 weeks to 7-10 (14), which is ~70% of 1RM in the last 4 weeks of the program.

Participants undertake additional group-based walking (“park walking”) exercises, progressing from 30 min at low-to-moderate intensities to 40 min at moderate intensities. These walking sessions are self-managed by participants based on the perceived effort and heart rate. Patients’ carers are invited to attend these sessions. These strategies (ie, leadership, independence, and carer involvement) are based on the theory of planned behavior [48] and are designed to change attitudes toward exercise, increase perceived behavioral control, and influence the subjective norms or the social factors. We believe that if patients find these sessions are enjoyable, the long-term adherence will be higher, and this will have a significant impact on the long-term study outcomes.

### Behavioral Intervention (PVS)

PVS is a 5-step structured intervention delivered in routine primary care for the promotion of healthy habits [23,24]. It is based on strategies promoted by the United States National Cancer Institute and the counseling and intervention group of the United States Preventive Services Taskforce for the clinical management of PA, diet, and alcohol [48]. These strategies are considered the minimum effective health care interventions to produce behavior changes. The participant goes through a process of change structured around the five As (assess, advice, agree, assist, and arrange) construct for clinical counseling: (1) assessment of the participant’s PA, diet and smoking habits, beliefs, and attitudes, (2) provision of evidence-based advice and graphical information on the benefits and risks of these habits, as well as exploration of the participant’s intention to change these habits, (3) reaching an agreement for an appointment with the clinician to discuss the changes, (4) assistance in the design of an individualized plan that overcomes the barriers reported by the participant, and (5) arrangement for continued follow-up and modification of the plan.

**Statistical Analysis**

Data will be analyzed on an intention-to-treat basis with the maximum likelihood imputation of missing values, comparing average change scores at 3 months of follow-up (postintervention) among participants randomly assigned to the Bizi Orain or PVS groups. These analyses will include standard descriptive statistics, Student *t* tests, and analysis of covariance models adjusted for baseline values. These models will be extended to include clinically relevant covariates. Subgroup analyses will be conducted by cancer site and treatment status. Investigations into responders and nonresponders will be conducted to explore the heterogeneity of the intervention effect. To analyze the association between changes in the PA over time and outcome variables, longitudinal mixed-effects models will be used for repeated measures throughout the 5 years of follow-ups. Cox proportional hazards models will be used for survival analysis. No imputation method will be used to handle missing data as longitudinal mixed-effect models based on maximum likelihood estimation are more appropriate to handle missing data [49] than common imputation methods such as the last observation carried forward, complete case analysis, or other possible forms of imputation.

Finally, the incremental cost-effectiveness, cost-utility ratios, and confidence intervals will be calculated through bootstrapping and sensitivity analyses. All the analyses will be performed with SAS (version 9.4, SAS Institute) and R (version 3.6, R Core Team) statistical packages.

We have a network of 6 exercise laboratories with a capacity to include at least 1013 patients during the 2 years of recruitment. Assuming a 30% rate of loss (including deaths) throughout the year of follow-up, the study has a power of 80% to detect a difference in functional capacity between comparison groups, of at least 9 s in the 400-m walk test at 3 months as significant (α=.05), assuming a standard deviation of 95 m. Regarding the quality of life, the study has a power of over 90% to detect differences of 5 points between groups as significant (α=.05).

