Despite the established benefits of exercise for patients with cancer and calls to include it as an integral part of cancer treatment, the chances of this information reaching patients are considerably reduced by the self-reported lack of knowledge among oncologists concerning how to properly promote and prescribe exercise [14,15] and paucity of translation strategies for integrating efficacious exercise programs into routine cancer care [16]. Unfortunately, only ~13% of patients with cancer meet international PA guidelines objectively measured with accelerometers [17].

Nonetheless, in recent years, community-based oncological exercise programs have been gaining prominence. LIVESTRONG at the Young Men’s Christian Association (YMCA) [18,19] is a community-based exercise program that has shown sustainable benefits in terms of physical function and self-perceived health. Our previous findings from the “Eficancer” study also indicate that exercising thrice a week during a 12-week individually tailored exercise program conducted at local health centers can improve quality of life and physical function, and these improvements are sustained over time [20].

Exercise program accessibility remains a challenge in implementing the international PA guidelines, but this challenge could be mitigated with strategies and pathways that connect patients with exercise-related resources and a well-designed behavioral intervention program to counteract the common barriers to exercise faced by patients with cancer during and after first-line treatments [21]. Further, the long-term effects on the PA levels, physical function, survival, and cost-effectiveness of large-scale community-based programs that are accessible and generalizable to a large proportion of patients with cancer (ie, administered in a standard supportive care setting) are unknown.

The main objectives of this study are as follows:

to examine the effects attributable to an exercise program on physical function, and quality of life, and adverse effects compared to health habit prescriptions, and to explore whether these effects vary by cancer type, stage and treatments, age, or sexto analyze the association between the actual exercise dose (ie, number of sessions and exercise intensity, objectively measured PA level with accelerometers) and measured outcomesto assess the cost-effectiveness of the program

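### A responder/nonresponder split on observed 3-month change cannot by itself show that the intervention effect differs between patients; use treatment-by-covariate interactions

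*Protocol article*

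**What the plan says.** The Statistical Analysis section of the protocol article sets the randomised comparison as "comparing average change scores at 3 months of follow-up (postintervention) among participants randomly assigned to the Bizi Orain or PVS groups", using t tests and ANCOVA adjusted for baseline, later extended with further covariates. Two sentences then deal with variation in effect. The first is "Subgroup analyses will be conducted by cancer site and treatment status". The second is "Investigations into responders and nonresponders will be conducted to explore the heterogeneity of the intervention effect". The article does not say which outcome or cutoff defines a responder, or whether one arm or both are classified.

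The first main objective in the Introduction includes the aim "to explore whether these effects vary by cancer type, stage and treatments, age" and sex. Program Design gives a 1:1 randomised comparator for the first 3 months. That group receives the PVS behavioural intervention and starts the exercise programme only after the postprogram assessments.

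**The concern.** The second sentence joins a method (sorting patients into responders and nonresponders) to a purpose (learning whether the intervention effect is heterogeneous). In the randomised window each patient is observed under one arm only, so no individual treatment effect is seen. What is seen is a change score, and it has at least four components: the effect of the programme, test-retest error at both visits, recovery or decline that would have happened anyway, and regression to the mean from an unusually good or bad baseline. Cutting that score at any point yields two groups, whether or not the programme works differently in different people.

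The first main objective is at stake. The subgroup sentence names cancer site and treatment status. For stage, age and sex, which the objective also lists, the responder investigation is the only heterogeneity method that the Statistical Analysis section names. If baseline features that go with a large observed change are reported as predictors of response, readers may take them as guidance on who benefits, when they may reflect baseline extremes and noise.

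**Working it through.** **Inputs from the article.** The sample size statement gives "a capacity to include at least 1013 patients during the 2 years of recruitment". It allows for 30% loss, deaths included, and claims 80% power. The target is a 9 s between-group difference on the 400-m walk at 3 months, with α = 0.05. The SD is 95, printed in metres although the outcome is in seconds. The text does not say whether it is the SD of a single score or of change.

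**Can the SD of 95 be trusted?** Reproduce the plan's own 80% first (two-sided test assumed).
- Evaluable per arm: 1013 × 0.70 / 2 = 354.55.
- SE of the difference at SD 95 s: 95 × √(2/354.55) = 7.14 s.
- Power: Φ(9/7.14 − 1.96) = Φ(−0.70) ≈ 24%, not 80%.
- SD that would give 80%: 9 / [(1.960 + 0.842) × √(2/354.55)] ≈ 42.8 s.

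The power statement is a separate matter. Here it shows only that 95 is not a safe value for the SD of change, so a range is needed. I use 30 to 95 s.

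**Responder shares with no heterogeneity.** Assume normal change scores (positive = faster), zero mean change in the PVS arm and exactly 9 s benefit for every patient in the exercise arm. For cutoff T and SD of change s:
- PVS share = 1 − Φ(T/s)
- Exercise share = 1 − Φ((T − 9)/s)

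| SD of change (s) | T = 0: PVS / exercise | T = 9 s | T = 20 s | T = 30 s |
|---|---|---|---|---|
| 30 | 50.0% / 61.8% | 38.2% / 50.0% | 25.2% / 35.7% | 15.9% / 24.2% |
| 42.5 | 50.0% / 58.4% | 41.6% / 50.0% | 31.9% / 39.8% | 24.0% / 31.1% |
| 60 | 50.0% / 56.0% | 44.0% / 50.0% | 36.9% / 42.7% | 30.9% / 36.3% |
| 73.6 | 50.0% / 54.9% | 45.1% / 50.0% | 39.3% / 44.1% | 34.2% / 38.8% |
| 95 | 50.0% / 53.8% | 46.2% / 50.0% | 41.7% / 45.4% | 37.6% / 41.3% |

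Example: T = 9, s = 30 gives 1 − Φ(0.30) = 38.2% in the PVS arm and 1 − Φ(0) = 50% in the exercise arm.

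Every cell shows responders and nonresponders in both arms, although the effect is identical in everyone. At T = 9 s, the PVS share is 76% (38.2/50) to 92% (46.2/50) of the exercise share. The between-arm difference, 3.8 to 11.8 percentage points, is the uniform 9 s shift on another scale. It is not the fraction of patients who benefit.

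**What the randomised arms can tell.**
- *Ratio of SDs.* With 354.55 per arm, the SE of the log ratio is about √(1/353.55) = 0.0532. The ratio detectable with 80% power is exp(2.80 × 0.0532) ≈ 1.16, under normality. If individual effects are independent of the change without the programme, this needs an SD of effects of √(1.16² − 1) ≈ 0.59 times the PVS SD, for example 25 s when the PVS SD is 42.5 s.
- *Interactions.* For a factor that divides patients into two equal halves, the SE of the difference between the two subgroup effects is twice the SE of the overall effect. If the plan's 80% power for 9 s were right, the detectable interaction would be 2 × 9 = 18 s. At SD 95 s the detectable main effect is 20.0 s and the detectable interaction about 40 s.

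**The case against.** The strongest reply is that the article states no classification rule. It names no outcome, cutoff or arm, and does not confine the analysis to exercisers. Response modelled by arm and covariate would fit the sentence, and such detail commonly belongs in an analysis plan that is not shown. The sentence also says only that heterogeneity will be explored, and no primary comparison or sample size depends on it. All of this is fair, and the missing definition is not the complaint. The complaint is that no cutoff lets a split on observed change, taken alone, estimate variation in effect, and an exploratory label does not alter what is estimated.

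Two stronger readings are tempting, and the document does not support either.
- A reader might infer that about half of untreated patients would be classed as responders by chance. The comparator is not untreated, since it receives PVS counselling. The 9 s is a between-group difference from the power statement, not an individual cutoff. Exactly half arises only at a cutoff of zero, and at 30 s the PVS share is 16% to 38%.
- A reader might infer that the trial cannot study heterogeneity at all. It can: a concurrent randomised comparator exists for 3 months, and nothing in the text rules out its use.

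It is also right that comparing SDs between arms is not decisive. The variance of change in the exercise arm equals the variance without the programme, plus the variance of the effect, plus twice their covariance. If those who would otherwise decline gain most, the SDs can be equal or even reversed despite real heterogeneity.

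**Conclusion.** The concern holds in this limited form: a responder/nonresponder split on observed 3-month change cannot by itself show heterogeneity of the intervention effect. This follows from the design and needs no particular cutoff. It does rest on reading response as observed change, which is the natural reading because change scores are the stated 3-month outcome.

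The size is illustrative: 38% to 46% of PVS patients against 50% of exercisers. It assumes a 9 s cutoff, a uniform 9 s benefit, no mean change under PVS, normality and an SD of change of 30 to 95 s. The primary comparison is unaffected. What is affected is the part of the first main objective that asks for whom the programme works.

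**What to change.** Replace the responder sentence with an exploratory analysis of treatment-by-baseline-covariate interactions in the planned baseline-adjusted ANCOVA at 3 months. Cover the factors in the first objective (cancer type, stage, treatment, age, sex) and report each interaction estimate with its 95% CI.

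If response proportions are reported, give them for both randomised arms with the same cutoff, interpret only the between-arm difference, and do not present it as the share of patients who benefit.

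A ratio of the SDs of 3-month change between arms, with 95% CI, may be added as supportive evidence, with a note that similar SDs do not exclude heterogeneity.

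The cost is a change of wording; no new data are needed. The drawbacks are that individual responder labels are lost and that interaction tests will have limited power, so wide intervals should be expected and a nonsignificant interaction should not be read as a uniform effect.

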### Program Design

Bizi Orain is a hybrid two-stage study. During the first 3 months, the study has a parallel-group randomized controlled clinical trial design, where study participants are randomly allocated (1:1) to either the Bizi Orain exercise program in addition to a previously reported behavioral intervention [23,24] for the promotion of healthy habits, or to the Prescribe Vida Saludable (PVS) group (In Spanish, “Prescribe Vida Saludable” means “prescription of healthy habits”) alone. After the postprogram assessments, participants allocated to the PVS group will initiate the Bizi Orain exercise program. Thereafter, a 5-year prospective observational cohort study will be conducted with follow-ups at 3, 6, 12, 24, 36, 48, and 60 months (Figure 1) to (1) examine the long-term clinical effects of PA exposure on overall survival, physical function, and patient-reported outcomes and (2) evaluate the feasibility of Bizi Orain, identifying potential barriers and facilitators for a generalized and sustainable exercise program within standard health care settings. To address this point, a qualitative research study will be conducted involving clinical, research, administrative, and community staff, and patients with cancer.

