#### Health Economics

An economic evaluation will be performed in parallel with the trial to assess the health benefits, additional costs, and potential savings of including exercise therapy as a standard of care for patients with cancer. This health economics analysis will provide the relative value for money of exercise medicine compared with other health care interventions in this patient population, stratified by age, cancer type, point along the cancer continuum, and stage of the disease. Hospital resource usage and associated costs will also be assessed to compare the costs of secondary health care utilization between the intervention and reference (usual care+PVS) groups. All hospital events, including emergency department attendances and admissions, outpatient visits and procedures, and inpatient admissions for all causes will be explored to quantify and identify potential disease-related events, as well as the total health care resource use for all other purposes inclusive of comorbidities and other chronic diseases. The cost of providing the supervised exercise and PVS interventions will also be quantified. Health benefits will be measured in terms of the quality of life based on the SF-6D utility index derived from the SF-36 and converted to a health utility score to obtain quality-adjusted life years for cost-utility analysis [40].

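### Bootstrap confidence intervals on cost-effectiveness ratios fail if the QALY gain is small relative to its standard error; net monetary benefit from the same bootstrap avoids this, and the usual-care comparator ends at month 3

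*Protocol article*

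**What the plan says.** The Statistical Analysis section of the protocol article fixes the economic summary: "the incremental cost-effectiveness, cost-utility ratios, and confidence intervals will be calculated through bootstrapping and sensitivity analyses". The Health Economics section describes an evaluation alongside the trial. Its utilities come from the SF-36 through the SF-6D, "converted to a health utility score to obtain quality-adjusted life years for cost-utility analysis", and it will "compare the costs of secondary health care utilization between the intervention and reference (usual care+PVS) groups". The same section plans value-for-money results by age, cancer type, position on the cancer continuum and stage. The Introduction lists cost-effectiveness among the main objectives.

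Program Design limits the randomised phase: "During the first 3 months, the study has a parallel-group randomized controlled clinical trial design". It then says "After the postprogram assessments, participants allocated to the PVS group will initiate the Bizi Orain exercise program", and a 5-year observational cohort follows. The article gives no expected utility difference, utility SD, cost figure, willingness-to-pay threshold or economic time horizon.

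**The concern.** A ratio of cost difference to QALY difference has a sensible interval only if the denominator stays clear of zero across the bootstrap replicates. When it does not, very different results share the same value. A replicate with cost +300 and QALY -0.0005 gives -600,000, and so does one with cost -300 and QALY +0.0005. The first is worse and dearer, the second better and cheaper. Percentile limits taken over such a mixture support no decision.

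The comparator raises a second issue. A usual care plus PVS arm exists only until month 3. After that both arms carry programme cost, and the contrast is immediate versus delayed exercise. A longer between-arm ratio under the first label would misdescribe what was compared.

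**Working it through.** The article has no QALY or ratio figure to reproduce, so the check asks when the planned interval breaks down.

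**Inputs from the article.** Randomised contrast 0.25 year; 1:1 allocation; capacity 1013; 30% loss. Evaluable: 1013 × 0.7 = 709, or 354.5 per arm. The Abstract reports 265 enrolled (the main Results section says 123); 265 × 0.7 = 185.5, about 186.

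**Assumed inputs, not in the article.** Utility SD 0.12; baseline correlation 0.7; linear change to month 3; cost difference 300 with SD 1500; cost and QALY errors independent; threshold 30,000 per QALY; a stratum holding a quarter of 709, or 177.

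**Formulas.**
- QALY difference = gap × 0.25 / 2 = 0.125 × gap.
- SE(QALY) = 0.125 × 0.12 × √(1 − 0.49) × √(2/n per arm) = 0.00080 at 709, 0.00157 at 186 and 0.00161 at 177.
- SE(cost) = 1500 × √(2/n per arm) = 113, 220 and 226.
- Share of replicates at or below zero = Φ(−QALY difference / SE).
- Ratio limits: 2.5th and 97.5th percentiles of simulated cost/QALY ratios.
- Net monetary benefit = 30,000 × QALY difference − cost difference, with SE √[(30,000 × SE(QALY))² + SE(cost)²].

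| Evaluable | Gap | QALY difference | Share ≤ 0 | Ratio, 95% limits | Net benefit, 95% CI |
|---|---|---|---|---|---|
| 709 | 0.01 | 0.00125 | 6.0% | −1.4 to 2.1 million | −488 to −37 |
| 709 | 0.02 | 0.0025 | 0.1% | 29,000 to 365,000 | −451 to 1 |
| 709 | 0.03 | 0.00375 | about 0% | 20,000 to 174,000 | −413 to 38 |
| 186 | 0.02 | 0.0025 | 5.6% | −0.67 to 1.1 million | −667 to 217 |
| 186 | 0.03 | 0.00375 | 0.9% | −51,000 to 425,000 | −629 to 254 |
| 177 (stratum) | 0.02 | 0.0025 | 6.0% | −0.71 to 1.14 million | −677 to 227 |

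The true ratio at a gap of 0.02 is 300 / 0.0025 = 120,000.

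**Sensitivity of the share at or below zero, 709 evaluable.**
- SD 0.08 to 0.15, correlation 0.7: 1.0% to 10.7% at a gap of 0.01, and at most 0.6% at 0.02.
- SD 0.12, no baseline correlation: 13.4% at 0.01 and 1.3% at 0.02.
- SD 0.15, no baseline correlation: 3.8% at 0.02.

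**Is the short duration the cause?** With the same linear form and a gap of 0.02 at 709, the QALY difference divided by its SE is 0.0025/0.00080 at 0.25 year, 0.010/0.0032 at 1 year and 0.050/0.0161 at 5 years. Each equals 3.11. Duration scales numerator and SE alike; gap, SD and sample size decide.

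**The case against.** A reader might infer that a 3-month contrast forces a QALY difference near zero and therefore makes the planned intervals uninterpretable. The article does not support that. It states no QALY effect, and smallness in absolute units is the wrong test, because what matters is the difference relative to its SE, which the horizon alone leaves unchanged. At the planned size and a gap of 0.02 or more, the interval is wide but readable under the main assumptions. If utility moved with the signal-to-noise implied by the article's claim of over 90% power for quality of life (z of at least 1.96 + 1.28 = 3.24), the share at or below zero would be at most 0.06%. All of this stands, and it makes the problem conditional.

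It can also be said that bootstrapping is standard, that sensitivity analyses are planned as well, and that planes, curves and thresholds often sit in a fuller economic plan. Bootstrapping is indeed not at fault, and the missing time horizon alone would be a detail that a journal article may leave out. What remains is that the article names confidence intervals on the ratios as the output. That choice is fragile at sample sizes the article itself makes foreseeable: the enrolment reported so far, and the planned strata.

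Finally, no passage says that the arms will be compared as exercise versus usual care plus PVS after month 3. That is correct. The labelling point is therefore a safeguard, not an error already made.

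**Conclusion.** The point holds as a conditional weakness in the stated economic summary, worth correcting before analysis. Under the assumed inputs, the ratio interval breaks down at a month-3 utility gap of about 0.01 with 709 evaluable, and at about 0.02 with roughly 180 evaluable. It does not break down at 709 evaluable with a gap of 0.02 or more, although that margin also narrows if the utility SD is larger and the baseline correlation is weak. Every utility and cost input is an assumption, so the thresholds would move with other values. What does not depend on them is the pooling of ratios of opposite meaning once replicates straddle zero, and the end of the usual-care comparator at month 3.

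**What to change.** From the same bootstrap, make incremental net monetary benefit with a 95% CI over a stated range of thresholds, plus a cost-effectiveness acceptability curve, the main expression of uncertainty, overall and in each planned stratum. Report the ratio as a point estimate, and attach an interval only when essentially all replicates have a positive QALY difference.

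Reserve the label of a comparison with usual care plus PVS for the randomised months 0 to 3. Describe any longer between-arm result as immediate versus delayed exercise, or as modelled or observational.

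The cost is a change of wording: no new data and no new resampling. The downside is that the randomised economic result is openly short-term and depends on a stated threshold range.

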**Results:**

A total of 265 patients have been enrolled into the study since January 2019, with 42 patients from the hematology service and 223 from the oncology service.

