## Results

A total of 123 patients have been enrolled into the study since January 2019, with 19 patients from the hematology service and 104 from the oncology service.

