Bizi Orain will add to our knowledge in clinical, epidemiological, and implementation fields by administering the program as a “real-world” intervention delivered in a standard supportive care service setting. The randomized controlled trial design of the study during the first 3 months will provide data on the impact of structured exercise on clinical outcomes. The large sample size allows for subgroup analysis, which may provide insight into how people with different cancer types and treatment statuses respond to exercise. Examination of the cost-effectiveness of the program represents a unique addition to the literature and significant advance in current knowledge regarding the potential value of cancer-specific exercise interventions to the health care system. The long follow-up period has the important goal of understanding the dose–response relationship between PA and mortality. Finally, qualitative analysis will help identify and overcome potential barriers toward developing a generalizable and sustainable exercise program as part of standard health care.

The major limitation of this study is possibly the length of the exercise program. It might not be the most appropriate design to evaluate the long-term benefits of regular exercise in terms of objectively measured and patient-reported outcomes and overall survival. On the other hand, Bizi Orain is an initial exercise program delivered in a standard health care setting that addresses patients’ needs during treatment or immediately after completion of the primary treatment, requiring greater supervision from qualified professionals owing to the number of adverse effects experienced at these times. Thus, delivering the program in a standard health care setting with qualified exercise physiologists, therapists, and nurses is appropriate. A second, community-based phase needs further investigation, but it could potentially contribute to maintaining higher PA levels, thereby reducing cancer-specific adverse effects and related comorbidities, resulting in a lower burden for health care systems, adding years to the lives of people with cancer, and most importantly adding quality of life to these years.

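### The 80% power for the 400-m walk pairs a difference in seconds with an SD in metres and cannot be reproduced; read as 95 s, the SD gives about 24%

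*Protocol article*

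**What the plan says.** Under Effectiveness: Primary Study Outcomes, the protocol article lists the 400-m walk, done in a 20-m corridor, among several measures of physical function. The sample-size paragraph at the end of Statistical Analysis starts from "a capacity to include at least 1013 patients during the 2 years of recruitment" and takes 30% loss, deaths included, over the year of follow-up. It then states that "the study has a power of 80% to detect a difference in functional capacity between comparison groups", and gives the target as "of at least 9 s in the 400-m walk test at 3 months as significant (α=.05), assuming a standard deviation of 95 m". Allocation is 1:1 (Randomization). The planned comparison is of 3-month change scores by t test and by analysis of covariance on baseline. The paragraph gives no baseline correlation, does not say whether the test is one- or two-sided, and does not say whether the SD is raw, of change or baseline-adjusted.

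On enrolment, the Results paragraph of the Abstract says "A total of 265 patients have been enrolled into the study since January 2019", while the Results section of the main text says "A total of 123 patients have been enrolled into the study since January 2019". Neither count has a cut-off date.

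**The concern.** Over a fixed distance the outcome is the time taken. The target difference respects that and the SD does not, so the ratio on which power depends is undefined as printed. Changing the unit alone does not repair the sentence: 9 against 95 is a standardised difference of 9/95 = 0.095, far too small for about 700 patients to detect with 80% power.

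This is the only power figure given for any physical-function outcome. A reader who meets a null result on the walk test will judge it against that 80%. If the true figure is much lower, a null result says much less about a 9 s effect than the article suggests.

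**Working it through.** **Inputs.** Total 1013, loss 30%, difference 9 s, SD 95 (printed in metres), α = 0.05 and stated power 80%, all from Statistical Analysis; 1:1 allocation from Randomization. Assumptions of this check: a two-sided test, and 95 read as seconds.

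**Evaluable patients.** 1013 × 0.7 = 709.1, or about 354.5 per arm.

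**Attempt to reproduce the 80%.**

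- SE = SD × √(2/n) = 95 × √(2/354.5) = 7.14 s.
- Difference/SE = 9/7.14 = 1.26.
- Power ≈ Φ(1.26 − 1.96) = Φ(−0.70) ≈ 0.24. The noncentral t also gives 0.24.

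**Other readings of the same figures (difference 9, SD 95).**

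| Reading | Two-sided | One-sided |
|---|---|---|
| 1013 total, 30% loss | 24% | 35% |
| 1013 total, no loss | 33% | 45% |
| 1013 per arm, 30% loss | 43% | 56% |
| 1013 per arm, no loss | 57% | 69% |

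A one-sample formula, which is not this design, gives 71% with 709 patients and 85% with 1013. No reading returns 80%. The 30% loss is stated for the year while the endpoint is at 3 months, so the relevant two-sided power with 1013 randomised in total lies between 24% and 33%.

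**What would give 80% with 709 evaluable** (1.96 + 0.8416 = 2.8016).

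- Detectable difference at SD 95: 2.8016 × 7.14 = 20.0.
- Largest SD at a difference of 9 s: 9 / (2.8016 × √(2/354.5)) = 42.8 s.
- If 95 s is a raw SD and ANCOVA is used, the residual SD is 95 × √(1 − r²). Setting this to 42.8 gives r = √(1 − (42.8/95)²) ≈ 0.89. For a change score, 95 × √(2(1 − r)) = 42.8 gives r ≈ 0.90. At r = 0.7, ANCOVA power is 42%.
- Sample size at 9 s and SD 95 s: 1750 evaluable per arm, 3500 in all, and 3500/0.7 = 5000 randomised.

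**Which figures fit together.** For a difference of 20 and SD 95, n per arm = 2 × (2.8016 × 95/20)² = 354.2. Rounded up to 355, the total is 710 and 710/0.7 = 1014.3, so 1015; without rounding, the total is about 1012. The article's 1013 lies between the two. The sample size, loss, SD and power are thus mutually consistent at a difference of 20, and 9 s is the figure that does not fit them.

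**Enrolment counts.** Abstract: 42 + 223 = 265. Main text: 19 + 104 = 123. Each sum is right, so the conflict is not a slip in adding up.

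**The case against.** The best defence is that the 24% rests on an SD the article never states. It prints 95 m, not 95 s. If the SD of walk time is about 43 s or less, or the baseline correlation is close to 0.9, then 80% for 9 s is correct and only the printed SD is wrong. This stands, and it is why 24% can be given only as a conditional figure. It does not rescue the sentence, because the article supplies neither that SD nor that correlation.

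A reader might infer that the metre sign is the error and that seconds were meant. The arithmetic does not favour that: with 95 kept, the other inputs fit a difference of 20, so the 9 s may be the stray figure. That too is inference, since no difference of 20 appears in the article.

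A reader might also infer from 265 or 123 enrolled that the trial ended far short and that its power should be recomputed at those sizes. The article does not support this. The 1013 is worded as a capacity, the counts are undated, and the Evaluation section says evaluation continues until the target size is reached. The final size is not known from the article.

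Nor is there a case against the claim of over 90% power for 5 points on quality of life. An article may leave the SD and scale to the full protocol, and with 709 evaluable the claim holds for any SD up to about 20.5. The Discussion's remark that "The large sample size allows for subgroup analysis" is no finding either, because heterogeneity of effect is framed as exploratory elsewhere in the article.

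**Conclusion.** The point holds in this form: the difference and the SD are in incompatible units, and the stated 80% cannot be reproduced from the article's own figures. If the SD is 95 s, power for 9 s is about 24% with 30% loss and 33% with none, and 80% power is reached only at about 20 s. These figures assume two-sided 0.05, 1:1 allocation, 1013 randomised in total and no gain from baseline adjustment. The near-exact fit at a difference of 20 suggests that the difference and the SD come from different calculations. The article does not show which is wrong, so it would go too far to say that the trial has 24% power or that a true 9 s effect would usually be missed.

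The sentence should be corrected before anyone relies on it. The 265 against 123 contradiction is a separate and lesser reporting error with no bearing on the power calculation.

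**What to change.** In the sample-size paragraph:

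1. Give the 400-m walk difference and SD both in seconds, with the source of the SD.
2. Say whether the SD is raw, of change or baseline-adjusted, and give the baseline correlation if one was used.
3. Restate either the power that 1013 patients with 30% loss give for 9 s, or the difference detectable with 80% power (about 20 s if the SD proves to be 95 s and no baseline adjustment is assumed).

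The sample size should not be raised in response. The fault lies in the stated inputs, the wrong one is not yet identified, and 1013 reflects the capacity of the exercise laboratories.

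Separately, replace the two enrolment counts with one figure and a cut-off date, used in both the Abstract and the Results.

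The cost is rewording one paragraph and correcting one count. Design, analysis and conduct do not change. The stated power may become less favourable, depending on which input proves wrong.
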